### Cross-sectional surveys

2.3

Multiple cross-sectional surveys have been conducted in 16 MNCH municipalities of all four provinces. The cross-sectional data will track the changes in health outcomes at the population level over the MNCH project period (2022, 2024, and 2025). Lot Quality Assurance Sampling (LQAS) was used to determine the sample size of the cross-sectional surveys. LQAS is used to assess a program by analyzing data produced by a small sample. LQAS recommends using 19 supervision areas (SA) as the primary data collection unit. In this survey, 19 barangays were randomly selected in each province. Barangays were selected using the Probability Proportional to Size (PPS) sampling method. The sample size of *n* = 19 and decision rule of *d* = 13 was selected to maintain *α* error of ≤10%, and *β* error of ≤10%. It is interpreted that 80% coverage is achieved when more than 13 positive responses out of 19 responses are recorded. In practice, on average, 10 households were surveyed per barangay, based on field feasibility. Starting from the first household, the enumerator moved in a predetermined direction, visiting households until eligible respondents from each target group were found. In barangays with fewer than 10 eligible households, enumerators surveyed adjacent barangays after consultation with a survey supervisor. In each province, the number of households assessed was 190. The midline and the endline surveys will assess trends of antenatal, delivery, and postnatal care from baseline, midline to endline. The same barangays will be revisited for the midline and endline surveys, with an adjusted sample size to enable trend analysis over time. Assuming that the proportion of 8 or more antenatal checkups (a recent recommendation by the Philippines government) at the baseline was 15.6%, we expect a total increase of 8% in the outcome for 4 years, a 2% annual increase from the baseline to the endline with significance level 5%, design effect of 2, and non-response rate of 10%. The minimum required sample size is 900 participants. Thus, 225 participants are included in each of the four provinces, and 56 participants in each of the 16 municipalities. Each Barangay is divided into segments containing a roughly equal number of households; a segment is then chosen at random. This process is repeated until approximately 11 to 12 eligible households are identified in each barangay.

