### Cross-sectional survey

3.2

A total of 720 households across four provinces were included in the baseline survey. The baseline data collection was conducted in July 2022 in East Samar/Leyte and in October 2022 in Northern/West Samar. The midline study was conducted in September 2024 (Table 1) and the endline study is scheduled for September 2025.

Exploratory data analysis will be conducted to calculate mean (SD) and percentages for all variables collected during different surveys. Descriptive statistics will be stratified by province (East Samar, West Samar, Leyte, and North Samar) and comparability across the four provinces will be tested using *χ*^2^ tests for categorical variables and Student’s *t*-tests for continuous variables. Key indicators will be selected to assess health service utilization during ANC, delivery, and PNC, family planning, and maternal and child nutritional status. These will include the proportion of women attending at least four ANC visits, receiving skilled birth attendance, obtaining postnatal care within 48 h of delivery, using contraceptives, and the prevalence of undernutrition among mothers and children under 5 years.

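### The 900 per cross-sectional survey assumes 8 points at 2 points a year over 4 years, but baseline to endline is about 3 years, which gives about 6 points

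*Protocol article*

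**What the plan says.** All references are to the protocol article.

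- **Section 2.3, effect assumption.** The proportion with eight or more antenatal checkups "at the baseline was 15.6" per cent, and "we expect a total increase of 8% in the outcome for 4 years, a 2% annual increase from the baseline to the endline". The calculation is made "with significance level 5%, design effect of 2, and non-response rate of 10" per cent. The result is a minimum of 900 participants, split into 225 per province and 56 per municipality. No power and no sidedness are given for this survey.
- **Section 3.2, dates.** "The baseline data collection was conducted in July 2022 in East Samar/Leyte and in October 2022 in Northern/West Samar", and "the endline study is scheduled for September 2025".
- **Section 2.4.2.** The span 2022 to 2025 is described as a study period of four years.
- **Baseline count.** Section 2.3 gives 190 households assessed in each province. Section 3.2 says "A total of 720 households across four provinces were included in the baseline survey", and the abstract also gives 720.
- **Key indicators in section 3.2.** "These will include the proportion of women attending at least four ANC visits". Eight or more visits, the outcome behind the sample size, is not named there.

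**The concern.** The sentence behind the sample size fixes three things: a total (8 points), a rate (2 points a year) and a duration (4 years). It ties the rate explicitly to the interval between baseline and endline. The survey dates allow only about 3 years. The likely slip is that 2022, 2023, 2024 and 2025 were counted as four years, when three years elapse between a 2022 survey and a 2025 survey.

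These surveys are one of the two main sources for the impact component in section 2.4.2. If the programme delivers exactly the 2 points a year that the plan assumes, the survey has much less chance of showing it than 900 suggests. A non-significant trend could then be read as lack of progress although the assumed annual gain had occurred.

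**Working it through.** **Elapsed time.** Taking mid-month dates:

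- 15 July 2022 to 15 September 2025: 3.17 years. Rise at 2 points a year: 2 × 3.17 = 6.3 points.
- 15 October 2022 to 15 September 2025: 2.92 years. Rise: 2 × 2.92 = 5.8 points.

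The working value is 6 points, 15.6% to 21.6%. The plan's value is 8 points, 15.6% to 23.6%.

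**Inputs.** From section 2.3: p1 = 0.156, p2 = 0.236, alpha 5%, "design effect of 2", non-response 10%. Assumed because not stated: two-sided test, 80% power, equal rounds.

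**Reproducing 900.** Standard two-proportion formula:

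n = [1.960 × √(2p̄(1 − p̄)) + 0.842 × √(p1(1 − p1) + p2(1 − p2))]² / (p2 − p1)²

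With p̄ = 0.196 the two roots are 0.5614 and 0.5585, and n = 385.3 per round. The continuity correction, n/4 × [1 + √(1 + 4/(n × 0.08))]², gives 410.0.

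- × 2 × 1.1 = 902
- × 2 ÷ 0.9 = 911

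Both are close to 900. Without the continuity correction the results are about 850 to 858, a poorer match. Two-sided 90% power gives 1,136 to 1,203, and one-sided 80% gives 669 to 729; neither fits. One-sided 90% without correction and with × 1.1 gives 925, a marginal fit.

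**Power at 8 and at 6 points.** Two-sided 5%, no continuity correction, effective numbers after dividing by the design effect of 2:

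power = Φ[(p2 − p1 − 1.960 × SE0) / SE1], with SE0 pooled and SE1 unpooled.

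For 405 per round (900 × 0.9 ÷ 2):

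- 8 points: (0.08 − 1.960 × 0.02790) / 0.02775 = 0.912, power 81.9%.
- 6 points: (0.06 − 1.960 × 0.02734) / 0.02726 = 0.235, power 59.3%.

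| Effective n, baseline v endline | Treatment of the numbers | 8 points | 6 points |
|---|---|---|---|
| 405 v 405 | 900 less 10% non-response, both rounds | 81.9% | 59.3% |
| 450 v 450 | 900 completed, both rounds | 85.7% | 63.8% |
| 360 v 450 | actual 720 at baseline, 900 completed at endline | 81.2% | 58.3% |
| 360 v 405 | actual 720 at baseline, 900 less 10% at endline | 79.4% | 56.5% |

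With a continuity correction the first row becomes about 79% and 56%. Under the marginal one-sided 90% variant, power at 405 per round falls from 89% to 71%.

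**Scale of the gap.** The same formula at 21.6% gives 659 per round, or 692 with continuity correction. After the design effect and non-response that is about 1,450 to 1,540 per round, against 900.

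**Baseline count.** 4 × 190 = 760, against 720 reported. With 405 at endline, an effective baseline of 380 instead of 360 moves power at 6 points from 56.5% to 57.8%.

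**The case against.** The best defence is that only the total enters a two-proportion formula, and the plan states the 8-point total as plainly as the annual rate. If 8 points is the target, 900 is right, and the 2 points a year is a gloss obtained by dividing by the wrong number of years. That stands. A reader might infer that 900 is simply wrong, and the document does not show this. It shows that one of rate, total or duration must give way.

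Several other stronger readings also fail.

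- **That the plan promises 80% and delivers 60%.** Section 2.3 promises no power. The only 80% is in section 2.2.3, for antenatal coverage in the quasi-experimental study. The figure used here is inferred from the reproduction of 900.
- **That baseline fell short of 900.** Section 2.3 derives the baseline from lot quality assurance sampling and says the later rounds have an adjusted size, so 900 was not the baseline target. At 8 points the smaller baseline costs little.
- **That midline is underpowered.** The calculation covers baseline to endline only; no claim is made for midline.
- **That four or more visits has replaced eight or more.** The list in section 3.2 is open, so leaving eight or more out of it does not exclude that outcome from analysis.

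Baseline and midline are also already complete. That limits what can change, but it does not remove the need for a correct assumption beside the sample size.

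**Conclusion.** The effect assumption is wrong as written. The 8 points, the 2 points a year and the survey dates are mutually inconsistent, and this follows from the document alone. At the stated rate the expected rise is 5.8 to 6.3 points.

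The cost in power is conditional. It rests on a two-sided 5% test and a design meant to have 80% power, which the article does not state but which reproduces 900. On that footing, power at 6 points is 56.5% to 63.8%, against 79.4% to 85.7% at 8 points. If the target really is 8 points, the sample size stands and only the annual rate changes.

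The mismatch between 760 and 720 is real but minor: it moves power by little more than one point.

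**What to change.** In section 2.3, choose one of two statements and give the power and sidedness used:

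1. A rise of 8 points over about 3 years, that is 8 ÷ 3 = about 2.7 points a year, with a reason for the faster rate. The 900 is unchanged.
2. A rise of 2 points a year, so about 6 points by endline, with power of about 60% at the planned size.

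Reconcile 190 per province (760) with the 720 in section 3.2, and use the actual baseline number in the power statement. In section 3.2, list eight or more antenatal visits explicitly beside four or more, since the survey was sized on it.

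The cost is a few sentences and a less favourable rate or power. No extra households are needed.

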### Process evaluation

2.4

Most evaluation studies have focused on the impact of ttC on improvements in key health indicators considered from conception to 2 years of age. However, most ttC evaluation studies lack information on the implementation process. For example, the ttCF model schedules 12 home visits by BHWs over a period of nearly 3 years (1,000 days) per household. Process evaluation of such a long-term intervention requires substantial time and effort to understand the program pathways. Currently, there is insufficient evidence to determine whether these home visits take place as scheduled and in the intended number. In addition, household visits by community health workers are not mandatory and are driven by limited incentives, without additional compensation. In South Africa, the coverage of household visits by CHW was not as high as 17%, and one to two households were visited per day per CHW (25). A process evaluation in Ethiopia of monthly household visits to pregnant and children under 2 years of age reported that only 28.2% of intervention mothers had a visit by community volunteers for nutrition counseling in the past 3 months (32). For counseling by CHWs to be effective, not only must project participants create health behavior changes for pregnancy, childbirth, and childcare, but also community health facilities must provide relevant quality services. These challenges may affect the sustainability of the ttCF program.

The process evaluation will characterize the process implementation of the ttCF program using the RE-AIM planning and evaluation framework: (1) reach; (2) impact/outcomes; (3) adoption; (4) implementation; and (5) maintenance. Since its development in 1995, the RE-AIM framework has been widely used to design and evaluate community-based health promotion programs. RE-AIM framework is one of the most used planning and evaluation frameworks across the fields of public health, behavioral science, and implementation science (26).

Process evaluation study using the RE-AIM framework allows the utilization of various data sources produced during the MNCH program implementation (27). Our process evaluation attempts to reveal the program impact pathways and factors that may explain the impact of the ttCF program on maternal and child health outcomes. Multiple data sources will be used to assess the process evaluation components including a quasi-experimental study, multiple cross-sectional surveys, monitoring and performance records, and qualitative data collection. World Vision Philippines/World Vision Korea will prepare annual and semi-annual performance reports for internal review and grant reporting. Those reports will be used to extract the relevant data by the research team. World Vision’s Excel-based ttCF monitoring form has been used in several countries globally. Table 1 describes the key outcomes for each construct of the RE-AIM framework.

**Table 1 tab1:** The overview of RE-AIM framework components to conduct timed and targeted care for families (ttCF) process evaluation.

Components	Example of evaluation questions	Eligibility	Methodology
Reach (Percent of participants among the eligible population)	Percentage of pregnant women enrolled in ttCF program among eligible mothers	Pregnant women or women with one or more children aged 0–23 months in 16 project municipalities	ttCF Monitoring records World Vision’s performance Report Records from Rural Health Unit (RHU)
Impact (Impact/effectiveness at the individual level)	Percentage of access to postpartum care services Percentage of Exclusive breastfeeding Percentage of Minimum dietary diversity among children 6–23 months of age	Pregnant women and mothers of children aged 0–23 months in 16 project municipalities	Secondary data of baseline survey (2022) Midline (2024) and Endline (2025) Survey Cohort surveys (2023–2024)
Adoption (Application rate of Project activities)	Percentage of BHW who actually performed ttCF home visits out of all community health workers in the project area	~2000 BHW in 16 project municipalities	ttCF Monitoring record World Vision’s performance Report Qualitative study (2024)
Implementation (The extent to which the project was actually executed compared to planning)	Number of households where BHW conducted home visit counseling Number of BHW who completed ttCF training	~2000 BHW in 16 project municipalities	World Vision’s Performance Report ttCF Monitoring records
Sustainability: (The extent to which Project activities continue)	Percentage of mothers who are satisfied with BHW’s counseling performance	Pregnant women and mothers of children aged 0–23 months in 16 project municipalities	Midline (2024) and Endline (2025) Survey Cohort surveys (2023–2024) Qualitative study (2024)

#### Reach (at the individual level)

2.4.1

Reach (at the individual level) is defined as the number or percentage of individuals enrolled in interventions out of the eligible population. As a measure of the “reach” component, the proportion of pregnant women who are enrolled in the ttCF program will be calculated for each of the 16 project municipalities, using the number of pregnant women extracted from the monitoring tool. The proportion will be calculated in percentages for each province or municipality. The data sources for “reach” component are monitoring records, performance reports, and records from RHUs.

#### Impact/outcomes

2.4.2

The “impact/outcomes” component will be measured mainly using cohort follow-up surveys and multiple cross-sectional surveys. The multiple cross-sectional surveys will be conducted 16 MNCH municipalities, 4 provinces (Northern, West, and East Samar, and Leyte) while the cohort survey will be conducted in six intervention and six comparison municipalities in two provinces (East and West Samar). The cross-sectional data will track the changes in population-level health outcomes over a four-year study period (2022–2025) and the cohort study will measure 1 year of program impact following the same study participants. The impact indicators of ttCF are antenatal, delivery, and postnatal service utilization and health and nutrition indicators among pregnant and lactating women and children 0–24 months of age. Each indicator will be measured in percentages or numbers and will be summarized for each province and municipality.

#### Adoption

2.4.3

Adoption is defined as the extent to which project activities are implemented by BHWs. The adoption components are mainly evaluated among ~2000 BHWs in 16 project municipalities to examine to what extent BHWs performed household visits according to the guidelines. The main indicators are the percentage of BHW who performed home visits out of all community health workers in the project area. Data will be extracted from monitoring records and performance reports.

#### Implementation

2.4.4

Implementation is defined as the extent to which the project was conducted compared to planning. The ttCF implementation will be assessed at the stage of training and household visits among ~2000 BHWs. According to the ttCF guidelines, pregnant mothers are supposed to have four visits, at delivery to 6 months of age four visits, and 6–23 months of age another four visits. We calculate the percentage of BHWs who completed ttCF training out of all BHWs. We are interested in the percentage of households with ever home visit counseling by BHW, households with timely visits and messages at pregnancy, postnatal, and up to 23 months of age. In addition to monitoring records, study participants at cohort and cross-sectional surveys will be asked how many times they had home visit counseling by BHWs since their latest pregnancy. The data will be presented by province and by project municipality, and further investigation is made if the dose delivered of ttCF at each municipality will be associated with health outcomes.

#### Sustainability

2.4.5

Sustainability is defined as the extent to which program activities continue. Study mothers will be asked for their satisfaction with ttCF visits, and self-efficacy in putting the messages into practice. A qualitative study will determine the facilitators and barriers to ttCF activities, service satisfaction, and areas requiring improvement. This study plans to conduct in-depth interviews (IDI) and focus group discussions (FGD) with mothers, family members and BHWs.

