Several limitations of the study should be acknowledged. During the implementation period, similar public health promotion programs were reported in parts of the comparison area, potentially influencing BHW activities. These external factors likely introduced contamination in estimating the ttCF impact. As a result, implementing a randomized controlled trial (RCT) or quasi-experimental design in real-world settings proved challenging. The study anticipates recruitment challenges in identifying pregnant women during the early stage of pregnancy. Since program impact is maximized when mothers are enrolled from early pregnancy, delayed recruitment may reduce the potential benefits of the intervention. Over 60% of enrolled participants joined with children aged 0–11.9 months, limiting exposure to the full ttCF package. Further Eastern Visayas has geographically isolated and disadvantaged areas, some intervention communities were not reached within the current study design. These limitations may affect the representativeness and generalizability of the findings across Eastern Visayas.

While most evaluation frameworks in maternal and child health programs were limited to examining the program impact, our RE-AIM framework considered a comprehensive, multi-layered process and evaluation using various data collection tools such as quantitative, monitoring records and qualitative data tools.

Since the ttCF program was the first ever introduced in the Philippines, our evaluation will determine the extent to which the program has achieved the intended health and nutrition outcomes and identify remaining gaps in reaching the targeted indicators. The mid-term impact data will inform practitioners and donors to make decisions on long-term program planning, funding, and sustainability after the program cessation. Qualitative findings can highlight individual and contextual factors that support or hinder BHW’s home visits and to what extent the newly introduced ttCF model is integrated into the existing community health system. By assessing program reach, adoption, and sustainability, our research contributes valuable evidence to implementation science in maternal and child health in Southeast Asia.

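### Sustainability is defined as activities continuing, but its stated measures capture acceptability and determinants of continuation, all within the project period

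*Protocol article*

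**What the plan says.** Sustainability is the fifth component of the process evaluation and part of the second study objective (section 2.1). It is defined twice in the same sense: "Sustainability is defined as the extent to which program activities continue" (section 2.4.5) and "Sustainability: (The extent to which Project activities continue" (Table 1).

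The measures attached to it are:

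- Table 1, as its example for this row: "Percentage of mothers who are satisfied with BHW’s counseling performance".
- Section 2.4.5, surveys: "Study mothers will be asked for their satisfaction with ttCF visits, and self-efficacy in putting the messages into practice".
- Section 2.4.5, qualitative work: "A qualitative study will determine the facilitators and barriers to ttCF activities, service satisfaction, and areas requiring improvement". Section 3.3 makes sustaining factors one of three overarching themes.

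Table 1 gives the sources for the row as "Midline (2024) and Endline (2025) Survey Cohort surveys (2023–2024) Qualitative study (2024"). The ttCF monitoring records are listed for Reach, Adoption and Implementation, but not for this row.

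The Discussion presents the component as one of the study's contributions: "By assessing program reach, adoption, and sustainability, our research contributes valuable evidence to implementation science".

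**The concern.** The definition asks a quantity question: how much of the activity is still going on? The stated measures answer other questions: are mothers content with the counselling, do they feel able to act on it, and what helps or hinders it? A programme can score well on all of these while fewer BHWs make visits or fewer scheduled visits are completed.

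The article's own account of the risk makes the mismatch more awkward. Section 2.4 says it is not known whether visits happen on schedule and in the intended number. It notes that visiting is not obligatory and is weakly incentivised, and ends by naming these challenges as ones that may affect sustainability. The threat described is visits not taking place, yet the component built to address it does not count visits.

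At stake is a named part of objective 2. Followed as written, the evaluation would report a result under the sustainability heading that does not measure the construct defined there.

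**Working it through.** The article gives no figure to reproduce. The check compares definition, measures, sources and dates.

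**1. Does any stated measure give the extent of continuation?**

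| Stated measure | Where | What it describes | Extent of continuation? |
|---|---|---|---|
| Satisfaction with counselling | Table 1, 2.4.5 | Acceptability | No |
| Self-efficacy in applying messages | 2.4.5 | Mothers' confidence | No |
| Facilitators, barriers, areas to improve | 2.4.5 | Determinants | No |
| Sustaining factors | 3.3 | Determinants | No |

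None of the four does.

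**2. When are the sources collected?** The project runs 2021–2025 (1.1.1) and home visits began in July 2023 (1.2). The cohort was surveyed in September 2023 and September 2024 (3.1). The midline survey and the qualitative work were in September 2024, and the endline is scheduled for September 2025 (3.2, 3.3). Section 2.3 itself places the cross-sectional survey years within the project period. No later collection is described. The month in which the project ends is not given, so this step rests on the stated years.

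**3. Is activity measured elsewhere?** Yes. Adoption (2.4.3) takes the percentage of BHWs who made home visits. Implementation (2.4.4) takes households ever visited and visited on time, and asks cohort and cross-sectional respondents how many counselling visits they have had since their latest pregnancy. Performance reports are a further source for both components in Table 1. The planned breakdown under Implementation is by province and municipality. No breakdown by calendar time is stated, and neither section assigns its data to sustainability. The survey count is cumulative from the latest pregnancy, so by itself it does not date the visits.

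**4. Must satisfaction fall if visits fall?** That depends on the denominator, which the article does not settle. Section 2.4.5 speaks of satisfaction with visits, which suggests visited mothers. The eligibility column of Table 1 covers all pregnant women and mothers of children aged 0–23 months in the project municipalities. Take assumed figures, for illustration only: the share of mothers visited falls from 80% to 30%, and 95% of visited mothers are satisfied throughout. Activity falls by (80 − 30)/80 = 62.5%.

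- Visited mothers only: the indicator is 95% at both times.
- All eligible mothers, with unvisited mothers counted as not satisfied: 0.80 × 0.95 = 76.0%, then 0.30 × 0.95 = 28.5%.

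So the indicator may miss the fall entirely or follow it in full. Under the second denominator it tracks activity only because coverage is folded into it, and a reader could not separate less visiting from less satisfaction.

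**The case against.** The strongest reply is that the evaluation should be read as a whole. Visit activity is measured under Adoption and Implementation, from monitoring records, performance reports and surveys, so a decline during the project need not go unseen. This stands. A reader might infer that the plan would hide falling visits, or that the monitoring database is the only place visits are recorded. The article supports neither.

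Second, the qualitative work addresses what makes activities last. Facilitators, barriers, sustaining factors and integration into the existing health system are reasonable things to study in an evaluation that ends with its project. This also stands, and the work should be kept. It explains why activity might continue but does not say how much does.

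Third, a reader might infer that a satisfaction percentage will be used to declare the programme sustained, or to settle decisions after it closes. The article sets no such rule. The Discussion sentence on sustainability after cessation has the mid-term impact data as its subject, not satisfaction. Nor does section 2.4.5 say that continuation means continuation after funding ends.

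Fourth, the Table 1 column is headed as examples, and a condensed article may leave further indicators to a fuller document. That would excuse a missing indicator. It does not remove the mismatch in what is stated: section 2.4.5 sets out its own measures for a defined construct, and they measure something else.

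Last, the suggested continuation measures resemble the Adoption and Implementation indicators. They do. What is added is the time axis, the assignment to sustainability and an explicit limit on the claim.

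**Conclusion.** The point holds as a mismatch between construct and measure within the sustainability component. The definition concerns the extent to which activities continue. The stated measures describe acceptability and determinants, and all dated collection lies within the project period. Taken alone, the component could look favourable without having measured continuation.

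The effect is confined to one of five process-evaluation components. It changes no sample size, impact estimate or comparison between intervention and comparison areas. It deserves correction because sustainability is a named objective and the Discussion says the study assesses it.

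The conclusion rests on the article's own definition, on the stated project years rather than a known closing month, and on the measures in section 2.4.5, Table 1 and section 3.3 being those intended. It does not depend on the illustrative percentages, whose result turns on an unstated denominator.

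**What to change.** In Table 1 and section 2.4.5:

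1. Add a continuation indicator from the existing ttCF monitoring records, and list those records as a source for the row. For example, by calendar quarter from July 2023 and by municipality: (a) the share of trained BHWs recording at least one ttCF visit, and (b) visits completed out of visits due among registered households. Through September 2025 this gives 2 + 4 + 3 = 9 quarters.
2. Use survey-reported visit counts as supporting evidence, noting that they are cumulative since the latest pregnancy.
3. Report satisfaction and self-efficacy as acceptability, and state whether the denominator is visited mothers or all eligible mothers.
4. Keep the qualitative work, described as determinants of continuation.
5. State that conclusions cover the funded period and that maintenance after project end is not assessed. Word the Discussion claim to match.

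The cost is a re-tabulation of records already being encoded, assuming visit dates are among the encoded fields, plus wording. No new data collection is needed. The sustainability claim becomes narrower, and the trend depends on how complete the paper register is. The Discussion acknowledges a lag between collection and processing, so the most recent quarters should be held back until encoding has caught up. Otherwise late paperwork would look like falling activity.
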